### Sample size and analytical plan

The study goal is to estimate the success rate of the dietary intervention, as well as the success rate of the two-stage approach. Dietary counselling alone will not exceed this degree of increase which was seen with supervised intake and meal provision, but there are no robust data to support an estimate of its effect. However, potassium supplementation at the dose proposed would very likely result in achieved potassium intake of > 90 mmol/day in all participants. A sample size of 100 participants will allow us to able to estimate both success rates to within a margin of error of at most 5%. At 4 weeks, there should be little loss to follow-up; however, we estimate this to be about 20% to be conservative. Thus, this trial will enrol 120 participants. Furthermore, there are no plans for additional analyses including subgroup. Multiple imputation will be done for any missing data.

The primary outcome is a simple proportion of the participants who are able to achieve an increase in potassium intake. Secondary outcomes of the proportion of participants with persistent adequate potassium intake at 52 weeks, and safety outcomes, will also be reported as proportions. For the secondary outcomes of change in sodium, potassium, and blood pressure, the mean differences will be calculated and reported, and a paired *t*-test will be used to compare for statistical significance. There will be no interim analysis.

The proportions will be summarized as absolute numbers and percentages. Continuous outcomes will be reported as mean (and 95% confidence intervals). A *p* value of < 0.05 will be used for the paired comparisons of the continuous outcomes (i.e. secondary outcomes of change in sodium, potassium and blood pressure).

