**Methods:**

We propose to do a clinical trial in two stages with an adaptive trial design. In the first stage, participants with high blood pressure and proven low potassium intake (measured on the basis of a 24-h urine collection) will get individually tailored dietary advice, reinforced by weekly supportive phone/email support. At 4 weeks, if there has not been a measured increase in potassium intake, participants will be prescribed an additional potassium supplement. Testing will be conducted again at 8 weeks, to confirm the efficacy of the potassium supplement. Final measurements will be planned at 52 weeks to observe and measure the persistence of the effect of diet or additional supplement. Concurrent measurements of sodium intake, blood pressure, participant satisfaction, and safety measures will also be done.

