## Methods

### Study design and setting

The study design is a single-centre, single arm clinical trial, with an adaptive design of two possible sequential interventions. For the dietary advice, this is outside the phases which apply to pharmacological trial regulatory description. The potassium supplement aspect could be considered as a phase 2, since, though approved for other indications, they have not been approved for hypertension. Focused and individualized dietary counselling to increase potassium intake will be the initial intervention amongst hypertensive individuals with low potassium intake. The aim of the study is to find the most effective intervention to increase potassium intake in this population. Since diet is the only recommendation in current clinical practice guidelines, this will be the initial intervention. Only in participants who do not achieve an increase in potassium intake, as measured on the basis of her 24-h urine potassium, as described below, will a potassium supplement be added. From a safety perspective, this was thought to be the most suitable study design. A comparison of a potassium supplement with a diet might result in a change in diet in patients randomized to a supplement, with possible safety issues in terms of hyperkalemia. Hence, the study design is a two-stage intervention, of dietary counselling, with the second stage of supplement only added to those in home the dietary counselling has been insufficient in increasing potassium intake (Figs. 1 and 2).

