#### Stage 2: Potassium supplementation

Patients who are not able to successfully increase their potassium intake at 4 weeks with dietary counselling will be enrolled into stage 2. They will receive oral potassium supplementation in the form of 50 to 100 mmol of potassium citrate (25 to 50 ml of the liquid elixir based on the achieved 24-h urinary potassium). For those whose urinary 24-h potassium remains < 60 mmol/day, the dose of the supplement will be 100 mmol/day, and for those whose 24-h urinary potassium is between 60 and 90 mmol/day, the dose will be 50 mmol/day. In the DASH trial, the diet itself provides 120 mmol/day of potassium; however, the average measured 24-h urinary potassium was 2757 mg/day (~ 71 mmol/day). Hence, we are aiming for a higher dose of supplement to achieve the target outcome.

This dose of potassium is well tolerated in hypertension (reported adverse events, at < 1% frequency and not different from placebo, are change in bowel habits, belching and flatulence, and abdominal cramps with the current wax matrix-based and microencapsulated or coated microcrystal-containing preparations with extended release characteristics) [9, 20]. There are no reports of hyperkalemia reported in trials using this dose in a similar population [9, 13]. Potassium at this dose and formulation has excellent (> 90%) bioavailability [20]. This dose of potassium also should be effective in increasing urinary potassium to desired levels. There is also no comparator in this study since it is not a randomized controlled trial. Since potassium is well tolerated in hypertension, there will be no special criteria for discontinuing or modifying allocated interventions.

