#### Ascertainment and follow-up plan

In order to minimize ascertainment bias, all patients, irrespective of the group, will have similar measurement schedule. Nevertheless, we will study the frequency of loss to follow-up and reasons thereof.

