### Measurements

The dietary intake of potassium will be assessed using 24-h collection of urine. There is a very close relationship overall between urinary potassium excretion and dietary potassium intake. There is a circadian variation [21] (more potassium excretion in the day than at night) which will be overcome with a 24-h urine collection. Twenty four-hour urinary sodium and creatinine (to assess for accuracy of collection) will also be measured for all participants at baseline, 4 weeks, and 52 weeks (end of study). In addition, participants who enrol into stage 2 will have an additional 24-h urinary collection and set of measurements at 4 weeks after initiation of the potassium supplement/dose escalation. Blood will also be collected at the same time points for measurement of kidney function and electrolytes (creatinine, sodium, potassium, total CO_2_, chloride). As an additional safety measure, serum potassium will be measured 1 week after starting potassium supplementation, 1 week after dose escalation, and 1 week post each re-dispensing visit. Blood pressure will be measured using automated oscillometric measurements and 24-h ambulatory monitoring. Additional assessment of adherence to supplement (apart from 24-h urine measures) will be made on the basis of returned pills/bottles. Patients satisfaction will be assessed using a simple 3 question survey (see supplementary material). Furthermore, all collected samples will be sent over to the laboratory for analyses. Any leftover samples will be discarded as medical wastes. There are no plans for subsequent or ancillary analyses for the future studies.

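### The two-stage success rate has no stated counting rule and only 4-week failures are retested at about week 8, while a single arm without a comparator cannot rank interventions or confirm the supplement's efficacy

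*Protocol article*

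**What the plan says.** All places are in the Protocol article.

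- **Goal** (Sample size and analytical plan): the trial is to estimate how often counselling alone succeeds, "as well as the success rate of the two-stage approach". The same section sizes the trial for both rates. Neither it nor Outcomes gives a time point or counting rule for the second. Outcomes defines success as above 90 mmol/day on the 24-h urine at 4 weeks (primary) and persistence above 90 at 1 year (secondary).
- **Schedule** (Measurements): everyone is measured at baseline, 4 weeks and 52 weeks. Beyond that, "participants who enrol into stage 2 will have an additional 24-h urinary collection and set of measurements", 4 weeks after the supplement is started or escalated.
- **Follow-up** (Ascertainment and follow-up plan): to limit ascertainment bias, "all patients, irrespective of the group, will have similar measurement schedule".
- **Design** (Study design and setting): a "single-centre, single arm clinical trial, with an adaptive design of two possible sequential interventions". Stage 2: Potassium supplementation adds: "There is also no comparator in this study since it is not a randomized controlled trial".
- **Aim** (Study design and setting): "The aim of the study is to find the most effective intervention to increase potassium intake in this population". The abstract's Discussion makes a similar claim.
- **Purpose of the later test** (abstract, Methods): "Testing will be conducted again at 8 weeks, to confirm the efficacy of the potassium supplement".

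**The concern.** There are two linked problems.

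**The two-stage rate.** After week 4, the next urine comes from failures only. A short-term two-stage rate can therefore be built in only one way: keep the week-4 successes as successes and add the failures who pass about four weeks later. A single 24-h urine varies from day to day, so some week-4 successes would fall below the threshold on a repeat and some failures would rise above it with no change in treatment. Under this count, failures get a second test and successes do not.

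**The claims.** The supplement goes only to people selected for a low week-4 value, on top of counselling, with no comparator. Their later rise combines the supplement's effect with day-to-day variation, regression to the mean and continued counselling. If the gain from the week-4 rate to the two-stage rate is credited to the supplement, part of that credit belongs to retesting.

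**Working it through.** **1. The plan's own figure.** The only figure attached to the two-stage rate is its precision: a margin of at most 5% with 100 participants. At 95% confidence the half-width is 1.96 × √(p(1 − p)/100), which is 9.8 points at p = 0.5. It is 5 points or less only for p up to about 0.07 or from about 0.93, so the stated maximum is not reproduced. That is a separate matter: precision says nothing about the counting rule examined here.

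**2. Algebra.** Let p1 be the proportion above 90 at week 4, s the proportion of week-4 failures above 90 at about week 8, and r the proportion of week-4 successes who would still be above 90 at about week 8.

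- Either-time rate = p1 + (1 − p1)s
- Same-time rate = p1·r + (1 − p1)s
- Difference = p1(1 − r)

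The difference is never negative and does not depend on how well the supplement works.

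**3. Size.** The documents give neither p1 nor r, and the sample size section says there are no robust data for the effect of counselling. The values below are assumptions.

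| p1 | r | Excess p1(1 − r) |
|---|---|---|
| 0.10 | 0.9 | 0.10 × 0.1 = 1 point |
| 0.30 | 0.7 | 0.30 × 0.3 = 9 points |
| 0.50 | 0.5 | 0.50 × 0.5 = 25 points |

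With p1 = 0.30, r = 0.7 and s = 0.8, the either-time rate is 0.30 + 0.70 × 0.8 = 86% and the same-time rate is 0.21 + 0.56 = 77%. The sample size section expects the supplement to bring very probably everyone above 90. With s = 1 the either-time rate is 100% by construction, while the same-time rate is 0.21 + 0.70 = 91%.

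**4. Simulation under assumed variation.** Usual intake on counselling is taken as normal with mean 70 and between-person SD 15 mmol/day, with a within-person SD of 10 to 25. None of these values is in the documents.

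| Within-person SD | Week 4 above 90 | Either-time, no supplement effect | Either-time, +40 mmol/day | Same-time, +40 mmol/day |
|---|---|---|---|---|
| 10 | 13.4% | 20.1% | 86.7% | 80.0% |
| 25 | 24.7% | 40.4% | 79.0% | 63.2% |

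The excess is 6.7 points at SD 10 (86.7 − 80.0) and 15.8 points at SD 25 (79.0 − 63.2). A second set of assumptions applied the entry limit of below 60 mmol, with usual mean 65, between-person SD 20, within-person SD 12 to 22 and a diet effect of +15 to +40 mmol/day. It gave an excess of 5.3 to 18.9 points.

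**5. What the week-8 test can show.** In the no-effect column, the share of week-4 failures who pass on repeat is (0.201 − 0.134)/(1 − 0.134) = 0.067/0.866 = 8% at SD 10, and (0.404 − 0.247)/(1 − 0.247) = 0.157/0.753 = 21% at SD 25. Some conversions would therefore occur with an inert supplement, and the design has no group from which to subtract them.

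**6. Aim against design.** Ranking interventions requires each to be observed in comparable people. Here counselling is given to everyone, counselling plus supplement only to those in whom counselling failed, and the supplement alone to nobody. The design can estimate the success rate of counselling and of the sequence. It cannot compare them as alternatives.

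**The case against.** - **A reader might infer that 4-week successes are never retested.** The documents do not support that. Measurements includes everyone at 52 weeks, Stage 1: Counselling keeps successes in follow-up for another year, and above 90 mmol/day at 1 year is a secondary outcome. They are missing only from the week-8 step.
- **A reader might infer that the two-stage rate is overstated as planned.** That goes too far. The article states no counting rule, and the full protocol, available on request, may contain one. A rate read at week 52 would be free of the asymmetry. An either-time rate is also a legitimate target for a sequential strategy if reported as cumulative success; it misleads only when read as the share above 90 at one time.
- **The sizes rest on assumed variances.** This is correct. The zero-effect case is a limit, and it runs against the plan's own expectation of near-universal success on the supplement. Only the sign and the formula are free of those assumptions.
- **No analysis credits the gain to the supplement.** The analysis section plans proportions and paired t-tests only. But the abstract's Methods gives confirming the supplement's efficacy as the purpose of the week-8 test, so the attribution is written into the plan.
- **The goal is already worded as estimation.** The sample size section does so, the lack of a comparator is disclosed, and a safety reason is given for not comparing supplement with diet. This defends the design, but not the stronger claims in Study design and setting and in the abstract.
- **The schedule statement says similar, not identical.** This is fair, and Measurements discloses the extra collection openly. It is loose wording rather than a serious contradiction, although the schedules differ on the primary measure at exactly the step that matters.

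**Conclusion.** The point holds in a conditional form for the rate and directly for the claims.

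If the two-stage rate is counted as success at week 4 or, among failures, at week 8, it exceeds the same-time rate by p1(1 − r). Under assumed p1 of 0.10 to 0.50 and r of 0.5 to 0.9 that is about 1 to 25 points, with 9 points at p1 = 0.30 and r = 0.7. The documents supply neither quantity, so the range illustrates what could happen and is not an estimate for this trial. The retest asymmetry does not touch the primary 4-week diet proportion.

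The statements that the trial will find the best intervention and confirm the supplement's efficacy at week 8 are wrong as written. This conclusion needs no numerical assumption: it follows from a single arm, no comparator, and a supplement given only to people selected for a low value while counselling continues.

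**What to change.** 1. In Study design and setting and in the abstract, restate the aim as estimating the success rates of dietary counselling and of the diet-then-supplement strategy. Remove the claims to identify the best intervention or method and to confirm the supplement's efficacy.
2. Label the week-8 result as the uncontrolled response of diet failures to diet plus supplement.
3. In Sample size and analytical plan, state how the two-stage rate is counted. Describe any either-time figure as cumulative (ever-success).
4. Report beside it, as the same-time two-stage rate, the proportion of all enrolled participants above 90 mmol/day at week 52, counted whatever their earlier results, with missing values handled by the multiple imputation already planned.
5. Reword Ascertainment and follow-up plan to agree with Measurements: common visits at baseline, 4 and 52 weeks, plus an extra collection in stage 2.

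**Cost.** This takes wording and one additional reported proportion, with no new visit or sample. The downside is that the week-52 rate also reflects a year of adherence and loss to follow-up, so it answers a longer-term question and may look less favourable. That is why it should accompany the cumulative figure rather than replace it.

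### With 100 participants the 95% margin of error on a success rate can reach 9.8 points, not the stated 5, and no confidence interval is planned for the primary proportion

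*Protocol article*

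**What the plan says.** All the relevant text is under Sample size and analytical plan in the protocol article.

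- The aim is to estimate two success rates: that of dietary counselling and that of the two-stage approach.
- One hundred participants are said to "estimate both success rates to within a margin of error of at most 5" per cent. No confidence level is attached.
- On counselling alone, "there are no robust data to support an estimate of its effect". On supplementation, the expectation is that the dose "would very likely result in achieved potassium intake of > 90 mmol/day in all participants".
- On the endpoint: "The primary outcome is a simple proportion of the participants who are able to achieve an increase in potassium intake". The Outcomes section places it at 4 weeks, when only diet has been given.
- On reporting: "The proportions will be summarized as absolute numbers and percentages". The sentence that follows gives 95% confidence intervals to continuous outcomes. None is named for a proportion.
- Loss to follow-up: "we estimate this to be about 20% to be conservative", with 120 to be enrolled.

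**The concern.** A margin described as a maximum has to hold at the least favourable success rate unless a range of rates is assumed, and the article assumes none for diet. At a rate of 50%, 100 participants give a 95% margin close to 10 points, about twice the stated figure.

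The trial has no comparator, and the article states no hypothesis test or power calculation for the primary outcome. Precision is therefore the whole justification for the sample size. A reader who trusts the stated margin would take an observed dietary success rate of 30% to mean 25% to 35%, when the 95% interval is about 21% to 39%. If the result appears only as a count and a percentage, nothing in the report corrects that reading.

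**Working it through.** **Inputs.** Evaluable n = 100 and a maximum margin of 5 points (Sample size and analytical plan). No dietary success rate is given, so the worst case p = 0.5 is used and a range is shown. No confidence level is given for the margin, so 95% is assumed, with other levels shown.

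**Formula.** Half-width = z × √(p(1 − p)/n).

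**Trying to reproduce the stated 5 points (n = 100, p = 0.5).** The standard error is √(0.25/100) = 0.050.

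| Confidence level | z | Half-width (points) |
|---|---|---|
| 95% two-sided | 1.960 | 9.8 |
| 90% two-sided (95% one-sided) | 1.645 | 8.2 |
| 80% two-sided | 1.282 | 6.4 |
| about 68% | 1.000 | 5.0 |

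The stated figure appears only at z = 1, that is, as one standard error. The choice of interval does not rescue it: at 50/100 the 95% half-width is 9.6 points by Wilson and 10.2 by Clopper-Pearson.

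**95% half-width by true rate (n = 100, normal approximation).**

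| Rate | Half-width (points) |
|---|---|
| 5% or 95% | 4.3 |
| 7% or 93% | 5.0 |
| 10% or 90% | 5.9 |
| 20% | 7.8 |
| 30% | 9.0 |
| 40% | 9.6 |
| 50% | 9.8 |

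**Where 5 points is reached.** Solve p(1 − p) = 100 × (0.05/1.96)² = 0.0651. This gives p = 0.070 or 0.930. The cut-offs are slightly more extreme with better intervals: at 93/100 the half-width is 5.2 points by Wilson and 5.5 by Clopper-Pearson; at 95/100 it is 4.5 and 4.8.

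**Other sample sizes at p = 0.5, 95%.**

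- All 120 enrolled: 1.96 × √(0.25/120) = 8.9 points.
- 120 × 0.8 = 96 left after the assumed loss: 1.96 × √(0.25/96) = 10.0 points.
- Size needed for 5 points: 1.96² × 0.25/0.05² = 384.1, so 385 evaluable. Allowing for 20% loss, 385/0.8 = 481.25, so 482 enrolled.

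**Could the dietary rate be presumed to be 7% or less?** The Stage 2 section cites an average of about 71 mmol/day in the DASH trial, and the sample-size text says counselling will not do better than supervised feeding. Take a normal distribution with mean 71 as an illustration. A rate of 7% above 90 mmol/day needs (90 − 71)/SD = 1.476, so an SD of about 13 or less. The article gives no SD. Assumed SDs of 20 and 30 give rates of about 17% and 26%, with margins of about 7.4 and 8.6 points. A rate below 7% is possible, but nothing in the article establishes it.

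**The case against.** The strongest points on the other side are these.

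- **No confidence level is stated, so 95% is the reviewer's assumption.** This is true. But 95% is the only confidence level the article names, the paired tests use p < 0.05, and 90% and 80% fail as well. The missing level is a second fault, not a defence.
- **The two-stage rate may be near 100%.** This stands for that rate: at 100/100 the Clopper-Pearson lower limit is 96.4%, well within 5 points. It does not save the sentence, which covers both rates. The primary outcome is measured at 4 weeks, before any supplement is given.
- **Counts and percentages describe a summary format and do not rule out an interval, which an analysis plan could supply.** This has some force, since no sentence forbids an interval. But the text does not defer the matter. It sets how proportions will be reported, then names intervals for means only, in a study whose stated goal is to estimate proportions. The text should be changed wherever the interval method is finally specified.
- **The 96 completers bring in a separate issue, and multiple imputation is planned.** This is fair. It moves the worst case by only 0.2 points, and the finding does not depend on it.

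**Conclusion.** The concern holds. The stated maximum margin of 5 points is false for 100 participants at 95% confidence: the maximum is 9.8 points (9.6 by Wilson, 10.2 by Clopper-Pearson). The likeliest explanation is that the standard error was taken for the margin. The claim is plausible for the two-stage rate if supplementation works as expected. It is unsupported for the dietary rate, which is the primary outcome.

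The figure of 9.8 rests on a 95% level and a rate of 50%. At rates between 20% and 50% the margin is 7.8 to 9.8 points, so the conclusion does not hinge on the exact worst case. Because this is the only justification given for the sample size, it must be corrected. The lack of a planned interval for the primary proportion compounds it.

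**What to change.** Replace the precision sentence with wording such as: *With 100 evaluable participants, the 95% margin of error for a success rate is at most about 10 percentage points; it is 5 points or less only if the rate is at least about 93% or at most about 7%.* Those cut-offs come from the normal approximation. If Clopper-Pearson is adopted, about 95% and 5% are safer.

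Add to the analysis text that the dietary and two-stage success rates will each be reported with a 95% confidence interval, by Wilson or Clopper-Pearson. A Wald interval should be avoided because it shrinks to zero width at 100/100, a result the article treats as plausible for the two-stage rate.

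The cost is two sentences and a less favourable statement of precision. Enrolment, visits and data collection are unaffected. The alternative, keeping 5 points for any rate, would mean 385 evaluable participants.

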### Outcomes

The primary outcome will be a successful increase in potassium intake to > 90 mmol/day as estimated from the 24-h urinary sample at 4 weeks. The secondary outcomes are persistence of increase in potassium intake (to > 90 mmol/day) at 1 year. For examination of safety, the following outcomes will be specifically examined: hyperkalemia (as defined as a serum potassium > 5.1 mmol/L) at 4 weeks after initiation of dietary counselling, at 1 and 4 weeks after starting potassium supplements, 1 week after dose escalation/dispensing, and at 12 months in everyone and gastrointestinal side effects (change in bowel habits, belching and/or flatulence; abdominal pain or cramps). Additional patient-reported adverse effects will also be measured and reported. Serious adverse events will be captured and reported as per regulatory requirements.

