### Adverse events

The qualified investigator will follow adverse events with start dates occurring any time after informed consent is obtained until 7 days (for non-serious adverse events) or 30 days (for severe adverse events) after the last day of study participation. At each study visit, the investigator (or designee) will inquire about the occurrence of adverse events (AE)/serious adverse events (SAEs) since the last visit and record in participant research record and case report form. Events will be followed for outcome information until resolution or stabilization. This trial is a low risk, non-invasive intervention, with minimal adverse events anticipated and hence anticipation of low rate of loss to follow-up. Nevertheless, hypertension is a chronic disease, and it is possible that the complete 1 year follow-up will not occur for all patients and has a built in 20% loss in the sample size estimation.

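### One blanket multiple-imputation rule in a single-arm trial leaves the success rates resting on an unchecked assumption about dropouts; they may be overstated, most of all the two-stage rate

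*Protocol article*

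**What the plan says.** The rule is one sentence in Sample size and analytical plan: "Multiple imputation will be done for any missing data". It exempts no outcome. The sentence before it says no additional analyses, subgroup analyses included, are planned. Ascertainment and follow-up plan promises only to study how often, and why, participants are lost.

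The design has no control group: "The study design is a single-centre, single arm clinical trial, with an adaptive design of two possible sequential interventions". The primary outcome is binary: "The primary outcome will be a successful increase in potassium intake to > 90 mmol/day as estimated from the 24-h urinary sample at 4 weeks". Its estimator is equally plain: "The primary outcome is a simple proportion of the participants who are able to achieve an increase in potassium intake". The 52-week persistence outcome and the safety outcomes are also to be reported as proportions. The success rate of the two-stage approach is named as a study goal next to that of diet alone.

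On the expected loss, the sample size section says of the 4-week time point, after noting that loss should be small: "however, we estimate this to be about 20% to be conservative". The Adverse events section concedes that "it is possible that the complete 1 year follow-up will not occur for all patients" and says the trial "has a built in 20% loss in the sample size estimation". So one allowance of 20% serves both time points.

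**The concern.** Standard multiple imputation assumes that, given the variables in the imputation model, those with a missing outcome resemble those with an observed one. Here that may fail in one direction. Someone who gives up the counselling or the supplement, or does not bring a 24-h collection, may well be less likely to have passed 90 mmol/day. In a randomised comparison, similar bias in both arms could partly cancel. In one arm it goes straight into the reported rate.

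Two features of this design sharpen the point.

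- Inclusion requires a 24-h urine potassium below 60 mmol and success requires more than 90. A participant with no 4-week collection therefore has only a non-successful value on record, and any imputed success is borrowed from people who stayed.
- Stage 2 is entered on the strength of the 4-week result. Someone lost by then never starts the supplement, yet a blanket rule could give that person a successful two-stage outcome.

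At stake is the trial's main product: the success rate of diet counselling and of the two-stage strategy. The wording also takes in hyperkalaemia and gastrointestinal side effects, where an imputed event is not an observed one.

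**Working it through.** **Inputs from the Protocol article**

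- Precision claim, with the margin put at 5%: "A sample size of 100 participants will allow us to able to estimate both success rates to within a margin of error of at most".
- Enrolment of 120 and loss of about 20% (Sample size and analytical plan).
- Success rate for diet: none given, because no robust data exist. Success on the supplement: expected in essentially all participants.

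**Assumptions, not in the article:** p_c of 20%, 50% and 95% as illustrations; p_d from 0 up to p_c.

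**Step 1: the plan's own figures.** The 95% half-width is 1.96 × √(p(1 − p)/n). At n = 100 and p = 0.5 it is 1.96 × 0.05 = 0.098, or 9.8 points. It is 5 points or less only for p ≤ 0.07 or p ≥ 0.93. The stated 5% therefore does not reproduce as a worst-case 95% margin; at p = 0.5 it equals one standard error. Enrolment of 120 is 100 × 1.2. A 20% loss from 120 leaves 96, and 100 completers of 120 would mean a loss of 16.7%.

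**Step 2: size of the overstatement.** Without informative predictors, imputation returns about p_c. The rate among all enrolled is (1 − d)p_c + d·p_d. The difference is

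d × (p_c − p_d),

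which is 0 if p_d = p_c, d·p_c if every dropout fails, and negative if dropouts do better.

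Overstatement in percentage points (all dropouts fail / dropouts succeed half as often as completers):

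| Loss d | p_c = 20% | p_c = 50% | p_c = 95% |
|---|---|---|---|
| 5% | 1.0 / 0.5 | 2.5 / 1.3 | 4.8 / 2.4 |
| 10% | 2.0 / 1.0 | 5.0 / 2.5 | 9.5 / 4.8 |
| 16.7% | 3.3 / 1.7 | 8.3 / 4.2 | 15.8 / 7.9 |
| 20% | 4.0 / 2.0 | 10.0 / 5.0 | 19.0 / 9.5 |

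For example, at d = 20% with all dropouts failing, 95% becomes 0.80 × 95% = 76%, and 20% becomes 16%.

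**Step 3: simulation check.** 1,000 trials were simulated, each with 120 enrolled, 24 missing, 20 imputations and no covariates. At p_c = 0.50 the mean imputed rate was 0.501, against 0.401 with dropouts as failures. At 0.20 it was 0.202 against 0.161; at 0.90, 0.900 against 0.721. These agree with the formula.

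**Step 4: when it is large.** At d = 20% the overstatement passes 5 points only if p_c − p_d exceeds 0.05/0.20 = 25 points. Against the 9.8-point half-width the gap must exceed 0.098/0.20 = 49 points. At d = 5% it cannot exceed 0.05 × 100 = 5 points.

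**Step 5: width of the bounds.** Best case is (1 − d)p_c + d; worst case is (1 − d)p_c. At d = 20% they are 16% to 36% for p_c = 20%, 40% to 60% for 50%, and 76% to 96% for 95%. Each range is d = 20 points wide.

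**The case against.** Five points can fairly be made for the plan.

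1. A reader might infer that imputation will overstate success by more than the claimed 5%. The article does not support that. It says nothing about how dropouts fare and gives no expected rate for diet. At 20% loss, a dietary completer rate of 25% or less keeps the gap within 5 points even if every dropout fails. The 5% is itself an unreliable yardstick (step 1). This objection stands, so the point is put conditionally.
2. Loss may be well below 20%: the article expects little at 4 weeks and calls 20% conservative. This also stands. Small loss shrinks the problem, but the analysis rule is fixed before the loss is known.
3. Imputation conditions on covariates. By week 52, earlier urinary potassium, sodium, blood pressure and adherence from returned bottles may be available, and the model may be set out in the full protocol or the SAP. This stands in part. Good predictors would reduce the bias, and the absence of a model from an article is no fault. But someone lost by week 4 has no post-baseline urine and no supplement record, so there is little to condition on.
4. Counting every missing collection as a failure is also an assumption, and it biases downward in a single arm. A lost or inaccurate collection does not prove low intake. This stands. It is a reason to show that analysis beside the imputed one, not a proof that it must be the main analysis.
5. A reader might infer that the plan intends to impute safety events. It does not say so; the Adverse events section describes asking about events at each visit. What remains is wording broad enough to include them.

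**Conclusion.** The concern holds in conditional form. The article applies one unqualified imputation rule to a single-arm trial whose results are proportions, and states no analysis that would show how far those results depend on it. The overstatement is d × (p_c − p_d). At 20% loss it lies between 0 and 4 points for a completer rate of 20%, between 0 and 10 for 50%, and between 0 and 19 for 95%, provided dropouts do no better than completers. The upper ends need both the full 20% loss and failure of every dropout. They are worst cases, not estimates of bias.

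The two-stage rate is the most exposed, for a structural reason as well as an arithmetical one: its expected value is near 100%, and those lost by week 4 cannot have succeeded on a supplement they never started. For the dietary primary outcome the effect may be small. The safety part is a matter of unclear scope.

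The conclusion rests on the blanket wording and the stated lack of additional analyses, not on missing detail about the imputation model.

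**What to change.** In Sample size and analytical plan, replace the single sentence with text that does the following:

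- Beside the imputed rate for each of the 4-week, two-stage and 52-week outcomes, report an analysis with all enrolled participants as denominator and those without a usable collection counted as not successful.
- Give best-case and worst-case bounds for the same three rates.
- State that success on the supplement is not imputed for a participant who never started it.
- Limit imputation to the efficacy outcomes. Report hyperkalaemia and adverse events on observed data, with the number assessed at each time point.
- Exempt these analyses from the statement that no additional ones are planned.

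The cost is a few lines of wording and one extra table, with no new data or participants. The reported success may look less favourable.
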